## Results

The DiPa study was funded in October 2019; received ethics approval on December 18, 2020; and was registered in the German Register for Clinical Studies on February 10, 2021. As of January 2021, the devices were assembled, and the stationary equipment (eg, the server, the NFC tags) was placed on the ward. Recruitment to the trial is finished, with a total of 12 participants having signed the written consent form by June 12, 2021. The measurements were initiated by giving out the first questionnaires.

The data assessment algorithms have been programmed, and the data assessment has been finished.

We expect to finish data analysis and publish the final results at the end of 2026 or beginning of 2027. We aim to publish the data and summary findings in academic journals and at conferences. For the participants, these will be presented accessibly in a staff meeting.

## Discussion

### Potential Outcomes and Impact

We aim to achieve results that provide deeper insights into the stress levels of nursing staff on the palliative care ward. A central focus is on identifying the causes of this stress. An essential part of the study deals with the investigation of various stressors, which include patient care, contact with relatives, working conditions, and the collegial working environment. Based on the studies by Diehl et al [6,11,31-33], we assume that the challenging task of dealing with seriously ill, dying patients and their death is a significant source of stress. In addition, based on the preliminary discussions with the participants, we expect that a considerable part of the stress is triggered by contact with the patients’ relatives. As a third important factor, we assume that the working conditions, including duty rosters, interaction with colleagues, and the number and timing of meetings, have a significant influence on the participants’ experience of stress. In order to record these and other relevant factors such as air quality or activities, a complex test design is required. Although questionnaires can ask about subjective feelings at a particular point in time, they are not able to take sufficient account of the day’s events as a whole or capture aspects that the participants may not be aware of—a well-known problem with the use of questionnaires.

To our knowledge, the DiPa project is the first innovative project addressing the burden on nursing staff in palliative care using wearable devices to collect objective data in combination with subjective measurement instruments such as questionnaires.

Since this project is the first of its kind, it aims to measure the feasibility of generating data with the abovementioned technology as a primary outcome. As secondary outcomes, we want to identify correlations between the recorded bioparameters and parameters of the work environment (time, telephone, temperature, etc) as well as subjective well-being, especially in handling sensor technology in a normal working day—which could be a potential stressor by itself.

### Strengths and Limitations

The content-related strengths lie mainly in two aspects: the multitude of measurements and the continuous measurement. As for the multitude of measurements, the study can assess all three aspects of the stress phenomenon: the stressors that elicit stress (activities, ambient conditions, noise, and interruptions—measured via smartphone, NFC tags, and Raspberry Pis), the stress reaction in the sense of subjective appraisal and feelings (measured via EMAs on the smartphone), and the stress reaction in the sense of the objective stress reaction (bioparameters, EDA, heart rate, HRV, and temperature measured via sensor hardware).

In addition, the study also features a methodological strength in the unobtrusiveness, interaction, and automation of the measurement devices: the smartphone and the sensor hardware were worn by the participants and were easily accessed. The sensor hardware was linked to the smartphone and sent data automatically; the smartphone in turn sent these data automatically to the server during the times when it was stored and charged in the lockers. This allowed for smooth data acquisition and increased motivation of the participants to collect data over such a long period and while working.

The study apparatus, for example, the use of smartphones or the scanning of the NFC tags, introduces a potential for user fatigue or confusion. The feasibility of sustained use was not assessed in this study, as the study did and does not intend sustained use of the apparatus. The assessment was deliberately limited to a duration of weeks to gain insights on the status quo of perceived stress, with a long-term goal of deducing provisions to reduce stress. However, the level of perceived fatigue caused by the interaction with technological devices, as well as the level of acceptance of technology and skill level when interacting with technology, could be assessed in future studies with a larger sample to allow for analyzing potential influences of these factors.

In the same line, introducing repeated prompts during the workday (the EMAs)—together with the aforementioned use of technology—can act as a further stressor. While this method enabled us to capture real-time self-reports of perceived stress and contextual factors, it may have inadvertently increased participants’ cognitive load or interfered with task performance, thus acting as an additional stressor. This reactivity to the assessment process itself could potentially amplify or confound the stress responses we aimed to measure.

Nonetheless, EMA offers critical advantages that justify its use. Unlike retrospective questionnaires, EMA minimizes recall bias and allows for the assessment of stress as it unfolds in the natural work environment, providing high ecological validity. This approach also enabled us to capture dynamic fluctuations in stress levels across the workday and to relate them temporally to physiological stress markers. Importantly, the combination of EMA and physiological measures enhances our ability to understand the complex interplay between subjective experience and somatic stress responses.

Still, the potential reactive burden introduced by the method should be treated as a confounding variable. To mitigate its potential confounding effect, the EMA protocol was designed to be minimally intrusive. The number of mandatory EMA prompts were limited to two per shift: one at the start and one at the end of the workday. Additional EMA entries were linked to the scanning of the NFC tags, enabling context-specific data collection while reducing the need for separate prompts. These intermediate assessments were optional and could be skipped without consequence if participants felt rushed, overwhelmed, or otherwise unable to respond at the moment.

Furthermore, we actively monitored the acceptability and perceived burden of the EMA procedure through qualitative feedback. Participants were interviewed midway through the assessment period and again at the end, where they were asked about the extent to which the EMA prompts were experienced as disruptive or burdensome. While a detailed analysis of this qualitative feedback is beyond the scope of this paper, these data are being prepared for publication in a separate manuscript focusing specifically on participants’ subjective stress perception, including their experiences with EMA in high-demand clinical settings.

Regarding the study population, the final sample (n=12) includes no stratified analysis plan based on shift, age, or prior burnout, limiting subgroup insights as a result of the study design. There is also a self-selection bias risk. Participants volunteered, likely introducing selection bias; for example, more tech-savvy nurses participated. However, we do not believe that only more resilient nurses participated in the study. Indeed, it is likely that interest in the study results and the resulting reductions in stress led to increased participation among a group of nurses who demonstrated even lower levels of resilience to stress.

Nurse shortages and the high emotional and physical demands of palliative care contribute to chronic workplace stress, which can undermine both staff well-being and patient care quality. Yet, traditional methods of stress assessment (eg, surveys and end-of-shift reports) often fail to capture the real-time, fluctuating nature of stress in these settings. By using digital monitoring tools such as EMA and physiological sensors, we aim to better understand the moment-to-moment stress patterns nurses experience during their shifts. This approach not only captures stress more accurately but could inform future targeted interventions or adaptive support systems, especially in the strained setting of palliative care where staffing and resilience are critical. The effects of these targeted interventions could then be evaluated by using similar methods to ensure comparability while adding measures for practical relevance such as stress-related attrition (eg, burnout or leaving the profession).

### Future Directions

In the near future, the results are to be used to derive preventive measures to reduce stress. While it is a scientific end in itself to gain knowledge on the stressors, we would like to use this knowledge to help enhance the working conditions and the well-being of the nursing staff.

For example, structural processes can be questioned and adjusted to reduce stress and its impact. The effectivity of these interventions will be part of further studies.

Parameters that measure stress have trained a multidimensional model. Based on the known input parameters (HRV, tonic and phasic EDA, and NFC labels) and knowledge of their correlation with stress (from the literature), it is possible to determine which factors primarily influenced the decision or outcome by visualizing the activation of neurons within the network. For regression, the architecture of a fully connected (dense) neural network will be used, with the goal of building a regression model that targets a value between 0 and 100%.

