**Methods:**

The nursing staff of an inpatient university palliative hospital ward gathered data over 6 weeks. Each was equipped with a smart wristband and a smartphone that continuously measure physiological and ambient parameters throughout their working day. These objective data were enriched by subjective measurements: a questionnaire at the beginning of the study that assessed multiple potential stressful situations and constellations in the private and working environment as well as ecological momentary assessments (EMAs) during the workday. The EMAs were prompted by scanning near-field communication (NFC) tags placed at different locations on the ward. The ongoing data analyses will be processed using computer algorithms partly programmed specifically for this study and partly drawn from existing libraries, such as toolboxes for neurophysiological signal processing for Python. Comparisons between subjective and objective measures and group comparisons between variables of interest will be made using inferential statistics, including regression analyses and analyses of variance. Data analysis using machine learning algorithms will be implemented once sufficient data are gathered.

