#### Preparation of the Hospital Ward

To assess possible stressors, NFC tags (Figure 2C) had been programmed and placed in numerous positions on the ward. The NFC tags were used to log the activity of the participants, such as NFC tags placed on the doors of the 9 patient rooms to log when a participant entered or left a specific patient room. Other activities that were logged included the beginning and ending of meetings (medical rounds; daily, weekly, and monthly team meetings; and daily handovers at the beginning or end of a shift), the beginning and ending of conversations with patients or their relatives, and relaxation.

Furthermore, in addition to pressing the wristband button, as aforementioned, a stressful event could also be marked by scanning the NFC tags, which offered the possibility to communicate a challenging situation by entering a short description of the current event using a Huawei smartphone P30 lite. This smartphone, which hangs by a cord around the participants’ necks and can be stored conveniently in their gowns’ pockets with the microphone poking out (see Figure 2A), was also used to measure ambient noise.

Last, 2 types of interruptions were measured, each with a microphone attached to a Raspberry Pi 4 Model B. The first was an interruption by telephone calls (eg, outsiders calling to reach patients or to retrieve information about the patients such as family physicians or calls from within the hospital, eg, calling about referrals). The second kind of interruption was a distress call (from a patient) or an emergency call (from a fellow nurse or physician), both broadcast through the hospital ward’s bell system.

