The acceleration data were fused to a 3D vector by applying the following equation:

All algorithms for data extraction were written in Python using Jupyter Notebooks and the *Pandas*, *Numpy*, *SciPy*, *Matplotlib*, and *NeuroKit2* libraries.

For stress detection analysis, all stress events marked with a button press will be identified, and windows surrounding this event will be extracted and averaged, leading to one value per stress event per participant. Analogously, the windows surrounding a scan of the NFC tag “relaxation” and the baseline windows will be extracted and averaged as well. Descriptive and inferential statistical analyses will be applied using IBM SPSS Statistics 30. Weighted ANOVAs for correlated samples will be computed to compare the stressful events and the baseline for each physiological parameter.

To examine the predictability of experiencing stress, the subjective ratings given in the EMA will be used as ground truth. Surrounding the EMA, data windows will be extracted from the data for each physiological parameter. A linear regression will be computed with the subjective stress level (EMA) as the dependent variable and entering the means of the physiological variables (HR, HRV, tonic EDA, phasic EDA, temperature, and acceleration) as independent variables. Artificial intelligence approaches will be used to analyze the data where appropriate.

With the data for daily occupancy of patients and the total number of nurses on the same day, we will be able to calculate the relationships of these 2 variables with stress. The minimum occupation level according to the recommendation from the German Society for Palliative Medicine (*Deutsche Gesellschaft für Palliativmedizin*) on staffing in palliative wards [30] of 1.4 nurses per patient will be used as a cutoff to create two subgroups of “well-staffed” and “under-staffed.”

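### Hidden-unit activations cannot rank stressors, and the listed network inputs omit acceleration and do not exclude the nurse's own stress-mark tag

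*Protocol article*

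**What the plan says.** The network is described in the Discussion under Future Directions: "the architecture of a fully connected (dense) neural network will be used, with the goal of building a regression model", with a target between 0 and 100%. Its inputs are given as "Based on the known input parameters (HRV, tonic and phasic EDA, and NFC labels". From these, together with literature knowledge of how they correlate with stress, the article says "it is possible to determine which factors primarily influenced the decision or outcome by visualizing the activation of neurons within the network".

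Data Analyses plans a separate linear regression of the EMA stress rating, "entering the means of the physiological variables (HR, HRV, tonic EDA, phasic EDA, temperature, and acceleration) as independent variables". NFC labels are not in that regression. The same section adds: "Artificial intelligence approaches will be used to analyze the data where appropriate".

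Preparation of the Hospital Ward says that NFC tags log room entry and exit, meetings, conversations and relaxation. It also says that "a stressful event could also be marked by scanning the NFC tags".

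**The concern.** Three features of the network plan bear on whether it can say what drives stress.

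- **Reading the network.** The activation of a hidden unit is an intermediate quantity. It is not the contribution of an input to the output.
- **Missing acceleration.** Movement can change sweat secretion and cardiac measures without any change in perceived stress, and it differs between ward activities. A model that sees EDA, HRV and activity labels but not movement can assign movement effects to those inputs.
- **The stress-mark tag.** If this tag is among the NFC labels, a nurse's declaration of stress is used to predict the same nurse's stress rating. The tag would then look like a leading factor without naming any stressor.

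The study wants to identify stressors and later to derive preventive measures from its results. A faulty attribution could point those measures at the wrong activities.

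**Working it through.** **What the article quantifies.** It gives no figure for the network: no performance, no number of EMAs and no variance components. The only related figure is participation, 12/18 = 66.7%, which reproduces the stated 67%. The checks below are therefore algebra, an illustration under stated assumptions, and a comparison of passages.

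**1. Do activations identify the factors?**

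Take a dense network with one hidden layer: h_j = max(0, w_j·x + b_j) and prediction f = Σ v_j h_j. The article does not name the activation function, so the rectified-linear form is an assumption. Choose any c_j > 0, replace w_j and b_j by c_j w_j and c_j b_j, and replace v_j by v_j / c_j. Then

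- the new activation is c_j h_j;
- the new prediction is Σ (v_j / c_j)(c_j h_j) = Σ v_j h_j = f.

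Numerical check: 500 random records, 4 inputs, 6 hidden units numbered 0 to 5, and c = (10, 0.1, 1, 5, 0.2, 2).

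- Largest difference in predictions: about 2e-15, which is rounding error.
- Units ordered by mean activation, before: 4,5,3,2,0,1.
- Units ordered by mean activation, after: 0,3,5,2,4,1.

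Two networks that are identical as predictors thus give different activation pictures. Exact rescaling is specific to this activation function, but the more basic point is not. Each w_j spreads over all inputs, so a large h_j does not say which input made it large. Without v_j it does not say whether the unit mattered to the output either. Literature correlations do not supply this information; they only suggest which answer to expect.

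**2. What can leaving out acceleration do?**

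| Variable | Linear regression (Data Analyses) | Network (Future Directions) |
|---|---|---|
| HRV, tonic EDA, phasic EDA | yes | yes |
| HR, temperature, acceleration | yes | not listed |
| NFC labels | no | yes |

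Illustration, with every setting assumed because the article gives none: 12 nurses with m EMAs each. Stress y = u + s has total variance 1, of which the nurse component u takes the share ICC. Acceleration a is standard normal and has no effect on stress. An activity label equals 1 when a plus standard normal noise exceeds 0.5, and it too has no effect on stress. Three physiological variables each equal a nurse level + 0.3s + 0.5a + noise. A linear model, used as a stand-in for the network, is fitted with and without a, 150 times per setting. Mean coefficient of the label, in SD of stress (true value 0):

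| m | ICC | without acceleration | with acceleration |
|---|---|---|---|
| 100 | 0.2 | -0.164 | 0.006 |
| 100 | 0.4 | -0.131 | 0.000 |
| 100 | 0.6 | -0.082 | -0.003 |
| 300 | 0.2 | -0.163 | -0.001 |
| 300 | 0.4 | -0.120 | 0.004 |
| 300 | 0.6 | -0.080 | 0.001 |

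The mechanism is simple. The physiological variables rise with both stress and movement. Without a, the label stands in for movement and is used to discount it, so an activity with much movement appears less stressful than it is.

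**3. Can the NFC labels encode the outcome?**

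Data Analyses takes the EMA rating as ground truth. Questionnaires describes it as a 0-100% slider for current stress, and the network targets the same range. The stress-mark tag is the nurse's own statement that a situation is stressful. Future Directions lists NFC labels without saying which ones. If this tag is included, input and target partly measure the same self-report. The size of the effect cannot be computed, because no counts of stress marks are given.

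**The case against.** The strongest reply has four parts.

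- **It is an outlook paragraph.** The text stands under Future Directions, the primary outcome is feasibility, and machine learning is conditional. The abstract says "Data analysis using machine learning algorithms will be implemented once sufficient data are gathered". This limits the weight of the point but does not remove it: Data Analyses also plans such methods, and the paragraph itself says "Parameters that measure stress have trained a multidimensional model".
- **The wording may be shorthand.** The authors may have a recognised attribution method in mind. That is possible, but the text names activations, and an unseen analysis plan would not make the sentence true as printed.
- **Two models may have different inputs.** This stands as far as it goes: the lists do not contradict each other. HR and HRV both derive from the interbeat intervals, and temperature is not a movement measure, so only the absence of acceleration carries the movement argument.
- **NFC labels belong in the model.** This stands. They are the only listed input that says what the nurse was doing, and the objection concerns one tag. Relaxation is listed as a logged activity, so it is not treated here as a self-report of stress.

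A reader might go further and infer that the network is bound to fail in a nurse outside the sample, or that its accuracy will be inflated because records of the same nurse fall in both training and test sets. The documents do not support either reading. They promise no prediction for other nurses and describe no data split, and validation details are commonly left to a fuller document.

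**Conclusion.** The point holds in three parts of different certainty.

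- **Activation claim: wrong as a method.** Activations do not measure the contribution of inputs and cannot rank stressors. This needs no assumption about the data.
- **Missing acceleration: a real risk of misattribution.** The range of -0.08 to -0.16 SD for a label with no effect rests wholly on the assumed settings and on a linear stand-in. It shows the mechanism and does not estimate the bias in this study.
- **Stress-mark tag: conditional.** Leakage occurs only if the tag is among the inputs, which the text leaves open.

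The change is worth making because the text offers the method as the way to find influential factors. The consequence is bounded: questionnaire, analysis of variance, regression and staffing analyses also feed the study's results, and the effectiveness of later measures is left to further studies.

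**What to change.** 1. Replace the statement about neuron activations with a named input-attribution method, for example permutation importance computed on held-out data, preferably with whole nurses held out.
2. Add acceleration to the network inputs. Align heart rate and temperature with the regression in Data Analyses, or give a reason for leaving them out.
3. State which NFC labels enter. Keep the activity labels and exclude the tag that marks a stressful event.
4. Describe the attributions as associations in these 12 nurses.

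Cost: wording changes and a little more analysis work. Holding out each nurse in turn would mean 12 refits. Reported accuracy may be lower once the stress-mark tag is removed and the model is assessed on held-out nurses. No new data are needed, since acceleration is already recorded.
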